### 2.2. Participants

The study will be carried out with diabetic patients from the Plasencia area. Participants who wish to participate in the present study must meet the following inclusion criteria: healthy type 2 diabetic patients between the ages of 50 and 60 years who are not taking medication for diabetes. Exclusion criteria will be established as having some underlying pathology (such as diabetic retinopathy or diabetic nephropathy), mobility disability and/or comorbidities incompatible with physical exercise and the use of vibration platforms, previous hip or knee surgeries, cognitive impairment, and neurological pathology.

Given the lack of studies that allow us to calculate the sample size for the sample to be representative, a pilot study will be carried out to obtain these data. A total of 40 subjects (20 men and 20 women) will be evaluated, divided into a control group (n = 20) and an experimental group (n = 20) (Figure 1).

### 2.3. Variables

Anthropometric measurements such as weight, height, and waist–hip ratio will be taken. In addition, functional tests such as Time Up and Go (TUG), 10 Meters Walk Test (10MWT), and 5 Sit To Stand (STS) will be performed. Finally, capillary blood samples will be taken to measure HbA1c and plasma glucose and lipid profile. In addition, blood pressure, weight, and height values will be collectd.

HbA1c is a blood test to determine the average level of glucose or sugar in the blood during the last two or three months [11]. According to the ADA for the diagnosis of diabetes, HbA1c should be at values greater than or equal to 6.5% (≥48 mmol/mol); however, normal HbA1c values should be below 5.7%. The Affinity A1c Analycer^®^ (Debramedix Slne laboratory, Spain)will be used. The HbA1c analysis is a simple test, which consists of obtaining a few drops of capillary blood from a fingertip using a lancet and transferring them to the Affinity A1c Analycer^®^. HbA1c will be taken at baseline and at 12 weeks post procedure to identify variations after VBW.

Regarding capillary glucose, it is a capillary blood glucose measurement using a glucometer (FreeStyle InsuLinx glucometer^®^, Abbott laboratory, Spain) to determine glucose values and facilitate self-monitoring of DM. Obtaining a capillary blood glucose sample is necessary to verify that participants are in optimal conditions to perform the training session (blood glucose levels lower than 90 mg/dl or higher than 250 mg/dl prevent participants from performing the exercises) and also to verify the effect of whole-body vibration (WBV) on the behavior of blood glucose 48 h after the previous session [11].

The LUX^®^ meter (Debramedix Slne laboratory, Spain) will be used for the quantitative measurement of blood parameters such as total cholesterol, HDL cholesterol, and LDL cholesterol (calculated). As with the HbA1c, it is a simple test, which consists of obtaining a few drops of capillary blood from a finger of the hand using an auto-lancet Vitrex Sterilance (Debramedix Slne laboratory, Spain) and pouring them into the LUX^®^ meter. The lipid profile should be below 200 mg/dL for total cholesterol, 40 mg/dL or higher for HDL cholesterol, and less than 100 mg/dL for LDL cholesterol and should be taken at baseline and at 12 weeks after the start of the procedure to identify variations after VBW [13].

Blood pressure is the force of your blood pushing against the walls of your arteries and will be determined with an Aneroid Sphygmomanometer (Riester, Jungingen, Germany). The values of this parameter considered normal are those situated at 120 mmHg systolic pressure and 70 mmHg diastolic pressure. Blood pressure will be a parameter, together with capillary glycemia, necessary to indicate whether the participants are in optimal conditions to perform the training session [14].

Height will be determined with a “Seca” (seca Deutschland, Hamburg, Germany) portable detachable stadiometer and weight with a Marsden M550 portable scale (Flintec Scales laboratory SL, Spain).

Anthropometric measurements will always be taken in the same space and at the same time, an early hour in the morning, keeping an ambient temperature between 20 and 22 °C.

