### 2.5. Procedure

Participants with type 2 diabetes will be recruited through talks, on alternate days, at the diabetic association of Plasencia (Cáceres). Those who wish to participate and meet the inclusion criteria will be contacted through a preliminary interview where they will be informed of the methodology, objectives, and process of the study and will be given an informed consent form that must be signed for their inclusion in the study. 

The screening will be performed by two physiotherapists and a research nurse at the University Center of Plasencia. The selected participants will undergo an interview where they will be asked about mobility disability and/or comorbidities incompatible with physical exercise in order to exclude those participants who do not meet the inclusion/exclusion criteria.

The study will be conducted from February 2024 to May 2024 by the aforementioned professionals. Participants will be randomly assigned to the intervention or control group, using a randomization list generated by a computer program. All participants who meet the above criteria will be offered entry into the study and will be given information and the schedule of interventions to participate in the study. Patients will continue with their usual lifestyle. After providing information about the study, they will be randomly included in one of the two groups (intervention or control).

Two of the researchers will be responsible for the correct control of the frequency and amplitude of the vibration platform during the entire intervention and for the correct performance of the exercises proposed for each training session, in addition to the functional tests TUG, 10MWT, and 5STS. A third researcher will be responsible for the determinations and parameters to be measured in the sample subjects (HbA1c and plasma glucose, lipid profile, weight, height, and blood pressure).

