#### 2.5.2. Experimental Group

Participants in the intervention group will be subjected to the following tests:-At the beginning of the intervention, a determination of glycosylated hemoglobin, blood pressure, lipid profile, weight, height, and TUG, 10MWT, and 5STS, which will be repeated after 12 weeks of intervention.-Before each training session, participants will undergo a basal blood glucose and blood pressure measurement, which will be repeated after the end of the session.-Each training session on the vibrating platform is composed of 6 exercises, with a duration of 60 s, with 60 s pauses between exercises and a warm-up exercise:

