### 2.6. Study Schedule

During the first week of February, detailed information on the procedure, informed consent, and the schedule of the study interventions will be provided. 

During the second week of February, preintervention measurements of HbA1c, lipid profile, blood pressure, height and weight, and TUG, 10MWT, and 5STS will be carried out so that they can be compared with the postintervention measurements.

During the following 12 weeks, the experimental group will carry out the intervention by means of the exercises in the WBV. These exercises will be performed three days a week, with a rest of at least 24 h between days of intervention.

In the third week of May, after the end of the intervention, the participants will again undergo HbA1c, lipid profile, weight, height, and TUG, 10MWT, and 5STS tests. The control group will also have their blood pressure measured (Figure 2).

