### 2.7. Statistical Analysis

A descriptive analysis will be performed for the experimental and control groups. Similarity between groups will be calculated at baseline and differences between groups at 12 weeks will be examined. The variables HbA1c, lipid profile, weight, height, and blood pressure will be selected in bivariate analyses. Adjustment for confounding factors will be examined by linear regression. Questionnaire scores will be assessed and changes between baseline and 12 weeks between groups will be sought. Statistical analysis will be performed using IBM SPSS statistics version 28.0.

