## 4. Conclusions

The whole-body vibration intervention for type 2 diabetics will allow testing of its influence on glycosylated hemoglobin and capillary glycemia levels, lipid levels after the intervention, as well as on blood pressure, body mass index, and functional balance. In addition, the aim is to test the effectiveness of the whole-body vibration platform as a method of physical exercise, improving patient adherence and its use in health centers.

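### Blood pressure is compared between arms but read on an observer-dependent aneroid device by a researcher who is likely to know the arm, so observer bias could appear as a vibration effect

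*Protocol article*

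**What the plan says.** Device: section 2.3 states that blood pressure "will be determined with an Aneroid Sphygmomanometer (Riester, Jungingen, Germany"). The same section also uses blood pressure as a check "necessary to indicate whether the participants are in optimal conditions to perform the training session".

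Measurer: section 2.5 states "A third researcher will be responsible for the determinations and parameters to be measured in the sample subjects", and its list of those measurements includes both plasma glucose and blood pressure. No other assessor is named for them.

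Contact by arm: under section 2.5.2, before each session, "participants will undergo a basal blood glucose and blood pressure measurement, which will be repeated after the end of the session". Section 2.6 gives the frequency: "These exercises will be performed three days a week", over 12 weeks. Section 2.5.1 has controls measured at baseline and at 12 weeks, living as usual in between, with no sessions and no sham platform.

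Use of the result: section 2.7 states "The variables HbA1c, lipid profile, weight, height, and blood pressure will be selected in bivariate analyses" and that "differences between groups at 12 weeks will be examined". Section 4 says the trial will test the influence of vibration on glycaemic and lipid levels, "as well as on blood pressure, body mass index, and functional balance".

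Blinding: section 2.1 calls the trial double-blind without saying which roles are blinded.

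**The concern.** With an aneroid gauge, the observer controls the deflation and decides which needle position to write down. Section 2.3 does not describe the reading technique, so this follows from the type of device. The other measurements assigned to the same researcher depend less on judgement: HbA1c, glucose and lipids come from analysers or meters, and weight from a scale.

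A reader who knows the arm and expects improvement can shift the recorded values of one arm by a few mmHg without intending to. Randomisation does not protect against this, because the error arises after allocation. Adjustment for baseline does not remove it either, because the session contacts begin only after the baseline visit and error by this route enters at the final reading. What is at stake is whether a blood pressure difference in the report reflects vibration or the person holding the gauge.

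**Working it through.** The protocol gives no SD, significance level, effect size or power for blood pressure, and section 2.2 presents the 40 participants as a pilot without a calculation. There is no stated figure to reproduce. The check has two parts.

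**1. Could the measurer stay blind?**

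- Sessions: 3 per week × 12 weeks = 36 per experimental participant (section 2.6).
- Session blood pressure readings: 36 × 2 (before and after) = 72 per experimental participant (section 2.5.2).
- Across the arm: 72 × 20 = 1,440 session readings, against none in controls.
- Section 2.5 lists glucose and blood pressure, the two quantities checked at sessions, under the third researcher.

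If that researcher takes the session readings, the arm is known long before week 12. The text makes this the natural reading, but section 2.5.2 does not name who takes them.

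**2. How much would a differential reading error matter?**

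Inputs: 20 per arm (section 2.2). Assumed: a two-sided 5% test, SD of 12-week systolic pressure 10 to 12 mmHg (wider range 8 to 15), no true effect, and one arm's readings shifted by *b* mmHg.

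- Standard error of the difference: SE = SD × √(2/20). SD 10 gives 3.16; SD 12 gives 3.79.
- Noncentrality: *b*/SE. For *b* = 2 this is 2/3.16 = 0.63 or 2/3.79 = 0.53.
- False-positive rate: probability that a noncentral *t* with 38 df exceeds the two-sided 5% critical value in either direction. Using 37 df, for a baseline-adjusted model, makes no material difference.

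| Assumed SD | SE | *b* = 2 | *b* = 3 | *b* = 5 |
|---|---|---|---|---|
| 8 | 2.53 | 12.0% | 21.2% | 48.7% |
| 10 | 3.16 | 9.5% | 15.2% | 33.8% |
| 12 | 3.79 | 8.1% | 12.0% | 25.0% |
| 15 | 4.74 | 7.0% | 9.5% | 17.7% |

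With *b* = 0 the rate is the nominal 5%.

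**Related inconsistency.** Section 2.5.2 repeats blood pressure at 12 weeks in the experimental arm. Section 2.6 leaves blood pressure out of its list of final tests and then names it for the control group only. If the experimental arm's final value were taken from a training session instead, the arms would also differ in measurement conditions.

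**The case against.** A reader might infer that the researcher must know the arm, having met each experimental participant at about 36 sessions. The documents do not say so. Section 2.5 allocates duties by variable, places the other two researchers at the platform throughout, and does not state that the third attends training. Section 2.5.2 names nobody for the session checks, which also serve to clear participants for exercise, so session staff could do them. The double-blind label, for what it is worth, points the same way, and a fuller protocol might name a blinded assessor. This part stands: knowledge of the arm is likely, not established. The concern still does not rest on silence, because the device and the person responsible for blood pressure are both stated choices.

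A reader might also take the table as evidence that the blood pressure result will be biased. It is not. The SD and the shift are assumed, and the table shows only what a given error would do. The largest rates need a one-sided error of 5 mmHg, for which the documents give no support.

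Three further points carry weight:

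- The objective in section 2 is HbA1c and blood glucose, both read off devices. Blood pressure is secondary in that sense, and section 2.2 calls the study a pilot. This limits the consequence.
- The three functional tests are run by the same two researchers who supervise training, and they depend on effort. That exposure is stated outright and may be the larger one, but it is a separate matter and does not make the blood pressure readings safer.
- An automated monitor leaves the operator in control of rest, cuff placement and repeat readings, and it does nothing about experimental participants being more used to being measured. So a change of device alone would be incomplete.

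**Conclusion.** The point holds in a limited form. The plan combines an observer-read device, one researcher responsible for all blood pressure readings, session checks in one arm only, and a control arm without sham, and it then compares blood pressure between arms. That leaves an open route for observer bias which the unexplained double-blind label does not close.

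Under an assumed SD of 10 to 12 mmHg and 20 per arm, a differential error of 2 to 3 mmHg would raise a 5% false-positive rate to about 8 to 15%. Over SDs of 8 to 15 mmHg the range is about 7 to 21%. Whether any such error would occur, and in which direction, cannot be shown from the documents. The HbA1c and glucose objective is much less exposed to this route. The change is worth making because it is cheap, not because the trial's main conclusion depends on it.

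**What to change.** In section 2.3, specify that the baseline and 12-week outcome readings of blood pressure are taken in both arms:

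- with the same automated monitor at both visits, since its values are not interchangeable with aneroid ones;
- under the same rest period, cuff placement and number of readings, fixed in advance;
- at the study visit, and not carried over from a training session;
- with every displayed value recorded.

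Reconcile section 2.6 with section 2.5.2, so that it is clear when and how the experimental arm's final blood pressure is taken.

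The cost is one monitor and a few sentences of text, with no extra staff or visit. The limitation is that an operator who knows the arm still controls positioning and timing, so the bias is reduced and not removed.

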**Timed Up and Go 3 m (TUG 3 m)**

This test will be performed with the use of a specific application (Mon4tic for IOS system). The cell phone is placed on the sternum by means of a special belt or held in place by the subject. The subject, seated with his back resting on the back of the chair (without armrests and height 43 cm), at the acoustic command following a five-second countdown, stands up, walks the expected distance, turns around a cone, goes back, turns 360°, and sits down again. The test time stops when the subject returns to the starting position and is completely immobile [15].

**10 Meters Walking Test (10 m)**

On command, the subject covers the distance walking as fast as possible, without running [16]. 

**Five times Sit To Stand (5STS)**

The subject will be seated with his back supported on the chair (without armrests and at a height of 43 cm) and, on command, stand up and sit down five consecutive times, as fast as possible and without using the push of the hands on the quadriceps. The arms may be crossed over the chest and subjects are instructed to stand up completely and not to lie down on the chair between repetitions [17].

These three tests will be implementd once on the same day (beginning and after each session) to avoid clinical changes.

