#### 2.5.1. Control Group

Participants in the control group will undergo a determination of glycosylated hemoglobin, blood pressure, lipid profile, weight and height, as well as functional tests such as TUG, 10MWT, and 5STS. Subsequently, they will be encouraged to continue their normal life, insisting on the importance of glycemic controls before and after their daily physical exercise, in addition to continuing with the dietary measures recommended by their specialist. After 12 weeks, glycosylated hemoglobin, blood pressure, lipid profile, weight, height, and the TUG, 10MMT, and 5STS tests will be redetermined.

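### The article times TUG, 10MWT and 5STS in two incompatible ways; read literally, one of them tests the experimental arm around every training session and the controls only twice

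*Protocol article*

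**What the plan says.** Two schedules for the three functional tests appear in the article.

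- **Section 2.3, end of the 5STS description:** "These three tests will be implementd once on the same day (beginning and after each session) to avoid clinical changes".
- **Section 2.5.2, experimental group:** a set of measurements at the start that includes "TUG, 10MWT, and 5STS, which will be repeated after 12 weeks of intervention". The measurements tied to each training visit are listed separately: "Before each training session, participants will undergo a basal blood glucose and blood pressure measurement", repeated when the visit ends. The functional tests are not in that second list.
- **Section 2.5.1, control group:** tested at entry, then "After 12 weeks, glycosylated hemoglobin, blood pressure, lipid profile, weight, height, and the TUG, 10MMT, and 5STS tests will be redetermined".
- **Section 2.6, study schedule:** in the second week of February "TUG, 10MWT, and 5STS will be carried out so that they can be compared with the postintervention measurements"; in the third week of May "the participants will again undergo HbA1c, lipid profile, weight, height, and TUG, 10MWT, and 5STS tests".

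Training is confined to one arm. Section 2.6 states "During the following 12 weeks, the experimental group will carry out the intervention by means of the exercises in the WBV" and "These exercises will be performed three days a week". Section 2.5.1 gives controls no training visits.

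**The concern.** The sentence in Section 2.3 attaches the functional tests to sessions; the other three sections attach them to two dated assessment visits. Nothing in the article says which governs.

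If staff follow Section 2.3 literally, the number of test attempts differs sharply between arms, because controls have no sessions. All three are timed performance tests, and the 10MWT and 5STS ask for maximal speed. It is plausible that such results improve with rehearsal, and rehearsal in one arm only would favour that arm. Tests taken just after squats and heel raises could also pick up fatigue or another acute effect, which need not act in the same direction.

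The outcomes at stake are the functional ones. Section 4 names functional balance among the effects the trial will test, and Section 2.7 compares the groups at 12 weeks. Extra practice given to one arm cannot be taken out in the analysis, so the point has to be settled before testing starts.

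**Working it through.** The article states no figure for the number of test occasions, so there is nothing to reproduce. The check is a comparison of the passages and a count.

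**1. What a session is.** Section 2.3 (glucose and blood pressure), Section 2.5, Section 2.5.2 with its warm-up description, and the Discussion all use the word for a visit on the platform. No passage uses it clearly for an assessment visit. Section 2.5 also gives the functional tests to the same two researchers who supervise training, so testing at every training visit would be practicable for a team that read Section 2.3 that way.

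**2. Inputs.** Duration: 12 weeks (Section 2.6). Frequency: 3 days a week (Section 2.6). Control occasions: 2 (Section 2.5.1).

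**3. Sessions.** 12 × 3 = 36 per experimental participant at full attendance.

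**4. Occasions per test for each participant, by reading.**

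| Reading | Experimental | Control |
|---|---|---|
| Sections 2.5.1, 2.5.2, 2.6: two visits | 2 | 2 |
| Section 2.3: once at the start, then after each session | 1 + 36 = 37 | 2 |
| Same, with separate baseline and 12-week visits | 36 + 2 = 38 | 2 |
| Section 2.3: before and after each session | 2 × 36 = 72 | 2 |
| Same, with separate baseline and 12-week visits | 72 + 2 = 74 | 2 |

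**5. Incomplete attendance.** The article gives no attendance figure. Assuming 50% to 75%, post-session occasions fall to 36 × 0.50 = 18 up to 36 × 0.75 = 27. With testing before and after, they are 72 × 0.50 = 36 up to 72 × 0.75 = 54. The imbalance against 2 remains.

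**6. Which values are exposed.** If the analysed values come from the February and May visits in Section 2.6, those visits lie outside the training period, so acute effects should not enter, but unequal practice would. If a post-session measurement serves as the final value, both enter.

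**The case against.** The strongest reply is that the procedural text points one way. Three sections fix two occasions, two of them separately by arm and one by calendar week. Section 2.5.2 draws a clear line between start-and-end measurements and per-session measurements, and puts the functional tests in the first group. Against this stands one parenthesis. The rest of that sentence, with its reference to a single day and to avoiding clinical change, fits a plan to do all three tests together on one assessment day, with *session* meaning an assessment visit. The sentence also speaks of the beginning, not of before each session.

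Most of this stands. It makes the two-visit schedule the likelier intention and means that per-session testing cannot be asserted as the plan. It does not remove the conflict: the sentence does not say two visits, and the article's own use of the word points to training.

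Three stronger readings are tempting and are not supported.

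- A reader might infer that each experimental participant is scheduled for exactly 72 extra repetitions of each test. That is one literal reading at full attendance; the literal range is 37 to 74, and under the other sections the count is 2.
- A reader might infer that this sentence alone prevents a functional gain from being credited to vibration. That attribution is unavailable anyway: the experimental arm performs six exercises on the platform while controls continue their normal life, so vibration and exercise are not separated even with equal testing.
- A reader might infer that the main result is compromised. The hypothesis and objective in Section 2 concern HbA1c and blood glucose, and rehearsing timed tests gives no practice advantage on HbA1c. The bivariate list in Section 2.7 does not name the functional tests.

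**Conclusion.** The contradiction is real and unresolved in the article. Its consequence is conditional: only if Section 2.3 is followed literally would the experimental arm take each test on about 37 to 74 occasions, at full attendance, against 2 in controls. Under Sections 2.5.1, 2.5.2 and 2.6 the arms are equal at 2 against 2.

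Under the literal reading, the between-group comparison of TUG, 10MWT and 5STS could be biased by unequal practice and, depending on which value is analysed, by acute effects of exercise. That rests on the plausible assumption that these timed tests respond to repetition. The article gives no practice-effect size, so neither the amount nor the net direction of the bias can be computed. The point is limited to the functional outcomes, which the stated objective does not name. It is still worth correcting, because the article says functional balance will be tested.

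**What to change.** In Section 2.3, delete the parenthesis from the sentence that follows the 5STS description. State instead that the three tests are done once at the baseline visit (second week of February) and once at the 12-week visit (third week of May), in both groups. This brings the sentence into line with Sections 2.5.1, 2.5.2 and 2.6, which need no change on this point.

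The cost is one sentence. No visit, measurement or familiarisation trial has to be added, and if any team had planned to test at training visits, the change reduces the work.

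### The article's Section 2.3 leaves the functional tests loosely fixed: no repeat attempts to average, an optional 5STS arm position, and a timing parenthesis that conflicts with the visit schedule

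*Protocol article*

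**What the plan says.** All of the following is in the protocol article.

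- **Occasions and attempts.** The 5STS paragraph of Section 2.3 closes with a sentence on all three functional tests that begins "These three tests will be implementd once on the same day". In full it reads: "These three tests will be implementd once on the same day (beginning and after each session) to avoid clinical changes". It mentions no practice attempt, no repeat and no rule for combining attempts.
- **5STS posture.** "The arms may be crossed over the chest and subjects are instructed to stand up completely". The one restriction on hands or arms is that the person rises "without using the push of the hands on the quadriceps". The chair (no armrests, 43 cm), the starting position with back support, and full standing are fixed.
- **TUG phone.** A second element is left open: "The cell phone is placed on the sternum by means of a special belt or held in place by the subject".
- **Schedule elsewhere.** Sections 2.5.1 (control) and 2.5.2 (experimental) give the three tests at the start and again after 12 weeks. Section 2.6 dates them to the second week of February and the third week of May. Around each training session, Section 2.5.2 lists only blood glucose and blood pressure.
- **Who tests.** Section 2.5 gives the functional tests to the same two researchers who control the platform and supervise the exercises.
- **Role of the tests.** The hypothesis and objective in Section 2 concern HbA1c and blood glucose. Section 4 says the trial will also allow testing of the effect on other measures, "as well as on blood pressure, body mass index, and functional balance".

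**The concern.** These are timed, fast-performance tests. The 10MWT instruction shows the type: "On command, the subject covers the distance walking as fast as possible, without running". If each is attempted once per visit, a slow start or a stumble becomes that person's value for the visit. With 20 people per arm there is little room to absorb such error.

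Optional posture is a separate source of variation, and it concerns the 5STS alone. A person could use the arms in February and cross them in May. The researchers supervising the test also run the vibration sessions, so they know who is in the experimental arm. Posture could therefore drift differently by arm, although nothing in the article shows that it will. The TUG phone position raises the same kind of question.

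The parenthesis about sessions matters for another reason. Only the experimental arm has sessions. Taken literally, that arm would practise the tests many times more than the controls, and a practice gain could pass for a treatment effect.

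**Working it through.** **Step 1: the passages side by side.**

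| Place | When the three tests are done |
|---|---|
| 2.3, 5STS paragraph | once, on one day, with a parenthesis naming the beginning and after each session |
| 2.5.1, control group | start and 12 weeks |
| 2.5.2, experimental group | start and 12 weeks; only glucose and blood pressure around each session |
| 2.6, schedule | second week of February and third week of May |

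Three places agree and one does not. Read literally, the parenthesis gives 12 weeks × 3 sessions = 36 sessions per person. With a test before and after each, that is 20 × 36 × 2 = 1,440 administrations in the experimental arm. The two-visit schedule gives 40 × 2 = 80 test visits in the whole trial. On neither reading does the text describe repeat attempts that are averaged.

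**Step 2: what averaging would gain.** The article has no calculation to reproduce: Section 2.2 sets 40 people without alpha, power, effect size or SD. The inputs below are assumptions, apart from 20 per arm.

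- r, reliability of a single attempt within a visit: 0.80 to 0.95.
- ρ, correlation of the true values at baseline and 12 weeks: 0.8 to 0.9.
- Errors independent between attempts; variance of a single attempt set to 1.

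The mean of k attempts has variance v = r + (1 − r)/k.

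*Plain comparison at 12 weeks, k = 2.*
- r = 0.80: v = 0.80 + 0.10 = 0.900, a 10% cut. √0.900 = 0.949, so the interval is about 5% narrower.
- r = 0.95: v = 0.95 + 0.025 = 0.975, a 2.5% cut. √0.975 = 0.987, so the interval is about 1% narrower.
- At 20 per arm and an assumed two-sided alpha of 0.05, the difference detectable with 80% power is (1.960 + 0.842) × √(2/20) = 0.886 single-attempt SD. It becomes 0.840 (r = 0.80) or 0.875 (r = 0.95). Power for a 0.8 SD difference rises from 71.6% to 76.0% or 72.6%.

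*Comparison adjusted for the baseline value.* The covariance between visits is c = ρr, and the residual variance is v − c²/v. For ρ = 0.9 and r = 0.80, c = 0.72 and c² = 0.5184. With k = 1 the residual variance is 1 − 0.5184 = 0.482. With k = 2 it is 0.9 − 0.5184/0.9 = 0.324.

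| ρ | r | k = 1 | k = 2 | Variance cut | Interval narrower by |
|---|---|---|---|---|---|
| 0.9 | 0.80 | 0.482 | 0.324 | 33% | 18% |
| 0.8 | 0.80 | 0.590 | 0.445 | 25% | 13% |
| 0.9 | 0.95 | 0.269 | 0.225 | 16% | 8% |
| 0.8 | 0.95 | 0.422 | 0.383 | 9% | 5% |

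**Step 3: which case applies.** Section 2.7 speaks of differences between groups at 12 weeks and of linear regression for confounding. It does not list the functional tests among its bivariate variables, and it sets no baseline-adjusted model for them. Both ranges must therefore be shown.

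**Step 4: posture.** The article gives no figure from which the effect of arm or phone position could be sized.

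**The case against.** The strongest objection is that the key sentence does not settle how many attempts are made. Its stated purpose is to avoid clinical changes, which fits doing all three tests together on one day. The number of timed attempts within that administration would then be unstated, and a condensed article may leave such detail to a full protocol. This stands in part. A reader might infer that the plan firmly fixes one attempt per visit. That is the likeliest reading, but the parenthesis stops it from being certain. What can be raised is what the text does state: the word once, the parenthesis that conflicts with three other sections, and the permissive wording on arms.

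Other limits also stand:

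- A reader might infer that loose posture affects all three outcomes. The arm-position wording touches the 5STS only, and most of the 5STS set-up is fixed. If each person uses the same posture at both visits, little within-person error results; the article does not require this.
- Clock stop points for the 10MWT and 5STS are not written out. They are detail that an article may omit, and the ends are implicit in covering the distance and completing five repetitions. They are no part of this point.
- A reader might take 9% to 33% as the size of the loss. That range needs a baseline-adjusted analysis that Section 2.7 does not set, and as interval width it is about 5% to 18%.
- A reader might infer that the experimental arm really will be tested around each session. Sections 2.5.2 and 2.6 do not support that.
- One practice and two timed attempts is one convention among several.

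**Conclusion.** The point holds as a modest one. Section 2.3 describes no attempts to average, leaves the 5STS arm position optional and gives a timing that contradicts Sections 2.5.1, 2.5.2 and 2.6. The first two add avoidable error to functional measures in a 40-person pilot.

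The loss recoverable by a second attempt is small in a plain 12-week comparison and moderate if the baseline value is adjusted for. Both ranges rest on assumed reliability, and the second also on an assumed correlation between visits. The contradiction in timing is the firmest part, since it needs no assumption.

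The documents do not support a claim of bias in the main comparison. The stated objective is HbA1c and glucose, and these tests lie outside it. That posture might differ by arm, because the testers know the allocation, is a risk and not a demonstrated effect. Severity: consider.

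**What to change.** Rewrite the closing sentence of the 5STS paragraph in Section 2.3 along these lines: TUG, 10MWT and 5STS are done in both arms at baseline and at 12 weeks only; at each visit the participant makes one practice attempt and two timed attempts of each test, with a short rest between them; the mean of the two timed attempts is analysed. Deleting the parenthesis about sessions brings the sentence into line with Sections 2.5.1, 2.5.2 and 2.6.

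In the same paragraph, require the arms to be crossed over the chest at both visits. In the TUG paragraph, choose one phone position, belt or hand-held, and use it for everyone at both visits.

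The cost is a few extra minutes at about 80 visits (40 people × 2), with the same staff, chair and walkway. The drawback is slight added fatigue, which the rest between attempts should handle.
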